#### Data analysis

The baseline characteristics of the participants were calculated using descriptive statistics. The between-group differences and 95% confidence interval (95%IC) for the post-treatment outcomes at 8 weeks and 16 weeks follow-up were calculated using linear mixed models using interaction terms of treatment group versus time. An intention-to-treat approach will be used in all statistical analyses. Per-protocol analyzes will also be performed, including only participants from the experimental group arm who adhere to the intervention (i.e., having performed at least 12 of the 16 training sessions). For the intention-to-treat analyses, the incomplete data (i.e., missing values) were estimated using multiple data imputation techniques through statistical software. All statistical analyzes will be performed using the SPSS statistical software (Statistical Package Social Science), version 20.0 for Windows (IBM corporation, Somers, New York, USA).

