
Eligible participants were randomly allocated to the intervention or control group with a 1:1 simple allocation using a computer-generated randomization sequence created by a blinded investigator via a random function in Excel software for Windows. After randomization, an independent researcher emailed each participant the login and password to access the specific app version to which they were allocated (intervention or control). Afterward, an assistant researcher inserted them into numbered, sealed, and opaque envelopes.

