### Statistical methods

#### Sample size calculation

Sample size estimation was performed a priori through G-Power’s statistical software (version 3) [53]. A sample size calculation determined that a minimum of 66 individuals would be required in the present study. Data used included 80% power to detect a between-group difference of 1.5 points in a 0 to 10 Pain NRS [54, 55], with an estimated standard deviation (SD) of 2.0 points [56], and a between-group difference of 4.0 points in a 1 to 24 points RMDQ [57], with an estimated SD of 4.9 points [58] and alpha error (two-tailed) of 5%. The estimated sample size would also allow for a loss to follow-up rate of up to 15% observed in studies involving similar populations (firefighters and military) and forms of intervention provision (i.e., app) [56, 59].

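### The stated group-by-time mixed model does not say how baseline pain and disability enter it; specifying baseline adjustment would gain precision at no cost

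*Protocol article*

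**What the plan says.** The Data analysis section states that the between-group differences and 95% confidence intervals at 8 and 16 weeks "were calculated using linear mixed models using interaction terms of treatment group versus time". It does not say whether the baseline measurement is one of the modelled responses, a covariate, or a mean held equal across arms. It also does not say which contrast from the model is the primary one.

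Baseline data exist. Study design lists three assessment points, including baseline, and the data collection section has the self-reported outcomes collected then. Under Outcome measures, the co-primary outcomes are pain intensity and disability at 8 weeks.

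The allocation paragraph, which follows the list of secondary outcomes, describes randomization "with a 1:1 simple allocation using a computer-generated randomization sequence". It names no blocking or stratification.

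The sample size section plans on a "between-group difference of 1.5 points in a 0 to 10 Pain NRS" "with an estimated standard deviation (SD) of 2.0 points", and on "a between-group difference of 4.0 points in a 1 to 24 points RMDQ" "with an estimated SD of 4.9 points". It gives a minimum of 66 participants and allows for up to 15% loss.

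**The concern.** A model with group, time and their interaction can give two different 8-week effects.

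- If only weeks 8 and 16 are modelled, the effect is the raw difference in 8-week means, which makes no use of baseline.
- If baseline is a modelled time point with its own mean in each arm, the interaction contrast is the difference in change from baseline. This subtracts the whole baseline value, although an imperfect correlation justifies subtracting only part of it.

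A baseline-adjusted analysis (ANCOVA, or a longitudinal model with a common baseline mean) weights baseline by how well it predicts the outcome, and so is at least as precise as either. At stake are the width of the confidence intervals for both co-primary outcomes and how far the estimates depend on a chance baseline gap. There is a further risk: the change contrast with a low correlation would have less power than the sample size section assumes.

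**Working it through.** **Inputs from the sample size section.** Pain difference 1.5, SD 2.0; disability difference 4.0, SD 4.9; "alpha error (two-tailed) of 5" per cent; 80% power; 15% loss; N = 66.

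**Assumptions not in the documents.** The correlation r between baseline and 8 weeks is 0.3, 0.5 or 0.7. The SD is the same at baseline and 8 weeks, except where varied below. The arms are of equal size.

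**Step 1: reproduce the 66.** Normal approximation for pain: n per arm = 2 × (1.960 + 0.842)² × 2.0² / 1.5² = 27.9, so 28 per arm and 56 in total; 56 / 0.85 = 65.9, so 66. Disability needs 24 per arm, or 48 in total, so pain sets the size. The 66 is therefore an unadjusted two-sample comparison that takes no credit for baseline. After 15% loss, 28 per arm remain.

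**Step 2: variance relative to the raw 8-week difference.**
- Raw difference: 1
- Change contrast: 2(1 − r), which is 1.40, 1.00 and 0.60 at r = 0.3, 0.5 and 0.7
- Baseline-adjusted: 1 − r², which is 0.91, 0.75 and 0.51

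Since 1 − r² = (1 − r)(1 + r), and 1 + r is below 2 when r < 1, the adjusted factor is below 2(1 − r). It is below 1 whenever r is not zero.

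**Step 3: power.** Two-sided 5% t-test (noncentral t), 28 per arm, SD multiplied by the square root of the factor.

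| Outcome | r | Adjusted | Raw | Change |
|---|---|---|---|---|
| Pain | 0.3 | 82.4% | 78.7% | 64.4% |
| Pain | 0.5 | 88.9% | 78.7% | 78.7% |
| Pain | 0.7 | 97.1% | 78.7% | 94.5% |
| Disability | 0.3 | 88.2% | 85.1% | 71.7% |
| Disability | 0.5 | 93.4% | 85.1% | 85.1% |
| Disability | 0.7 | 98.7% | 85.1% | 97.2% |

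The half-width of the 95% interval for pain is 1.96 × 2.0 × √(factor × 2/28). That is 1.05 points raw; 1.24, 1.05 and 0.81 for change; and 1.00, 0.91 and 0.75 adjusted.

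**Step 4: chance imbalance.** With 33 per arm and a baseline SD of 2.0, the SE of the baseline pain difference is 2.0 × √(2/33) = 0.49 points. A gap above 0.5 points in either direction has probability 31%. With equal SDs, a baseline gap g moves the raw difference by +r·g and the change contrast by −(1 − r)·g. For a gap of one SE, at r = 0.3, 0.5 and 0.7, that is +0.15, +0.25 and +0.34 points for the raw difference, and −0.34, −0.25 and −0.15 for the change contrast. Adjustment removes this dependence.

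**Step 5: simulation check.** In 300 simulated trials with three time points, 28 per arm and r = 0.5:

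| Estimate | SE | Slope on the baseline gap |
|---|---|---|
| Interaction contrast | 0.55 | −0.54 |
| 8-week difference | 0.53 | +0.46 |
| Common-baseline model | 0.46 | −0.04 |
| ANCOVA | 0.47 | −0.03 |

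**Step 6: smaller baseline SD.** Entry requires pain of at least 3 points, which may narrow the baseline spread. Suppose the baseline SD is 1.5 and the 8-week SD stays at 2.0. The change variance is then 1.5² + 2.0² − 2·r·1.5·2.0 = 4.45, 3.25 and 2.05, and power for the change contrast is 74%, 86% and 97%. Adjusted power stays at 82%, 89% and 97%. The SE of the baseline gap falls to 0.37, and a gap above 0.5 points has probability 18%.

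**The case against.** The strongest reply is that the article is condensed and an analysis plan may exist. One sentence about interaction terms does not exclude a baseline covariate. The same group-by-time model with a common baseline mean is essentially ANCOVA, and nothing in the text rules that out. This stands: a reader might infer that the plan uses only group-by-time terms and refuses adjustment, but the article does not say so. What remains is that the article does state the effect model for both co-primary outcomes, and its plain readings are the two less precise ones.

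A reader might also infer that baseline imbalance biases the estimate. It does not. Under randomization the imbalance averages to zero and is already in the standard error; its effect is conditional on the gap that occurs. Nor is it simply left in under the change contrast, which over-corrects for it.

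Nor do these figures show that the trial is too small without adjustment. With the raw 8-week difference, 56 completers give 80.1% power for pain by the normal approximation that reproduces the 66, and 78.7% by the t-test.

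Finally, a reader might want occupation added as a covariate because allocation was not stratified by it. The text gives no ground for this: Study setting and eligibility criteria groups police officers and firefighters as sharing exposure to factors linked with low back pain, and nothing shows that occupation predicts outcome.

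**Conclusion.** The point holds as one of efficiency and specification. The model as stated is valid; what it leaves open is how baseline is used. At the assumed correlations of 0.3, 0.5 and 0.7, adjustment cuts the variance by 9%, 25% and 49% against the raw difference. Against the change contrast with equal SDs, the cut is 35%, 25% and 15%.

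The case that matters most is the change contrast with a correlation below 0.5 and equal SDs, where power for pain falls below the planned level. At 0.3, by the plan's own normal-approximation method, 95 people would have to be enrolled for 80% power (80 / 0.85). At 0.7, adjustment gains little over change (97.1% against 94.5%), and with a baseline SD of 1.5 the two are practically equal there. All these sizes depend on the assumed correlation and SDs. The ordering does not: with the usual linear model, the adjusted estimate is in theory never less precise than either alternative, apart from the negligible cost of estimating one coefficient.

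**What to change.** For each continuous outcome measured at both follow-ups, model the 8- and 16-week values with that outcome's baseline value and its interaction with time as covariates. Alternatively, keep baseline as a response and constrain its mean to be equal across arms. For continuous outcomes measured only at 8 weeks, the baseline value alone is the covariate. Name the adjusted 8-week difference as the primary estimate for pain and for disability. If an existing analysis plan already says this, a sentence in the article pointing to it is enough.

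The cost is one line of model specification and no new data. Recruitment ended in May 2023, so the choice should be fixed and dated before outcomes are compared by arm. If that comparison has already been made, report the adjusted analysis as a declared change.

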#### Monitoring

##### Data monitoring and auditing

The study does not have a data monitoring committee either planned auditing trial conduct due to limited resources. We believe this committee would not be mandatory due to the characteristics of interventions and outcomes despite its high value for the overall trial quality. Interim analyses will not be conducted in this trial.

##### Harms, ancillary, and post-trial care

The adverse events were collected by weekly recording the number of adverse events throughout the intervention period. A closed-ended question with two options (yes or no) sent by the app at the end of each week: “During the last week of the study, did you present any different symptoms or worsening of the initial condition?”. Also, in case of a positive answer, a second closed question was asked: “Do you think this symptom or worsening of the initial condition was generated by the treatment provided in this study?”.

At least two researchers discuss all adverse events: the main researcher ([name]), the study manager ([name]), and medical consultants and experts if necessary. If the treatment is causing the participant to deteriorate, a video call is offered with one of the study physiotherapists to evaluate the issue or suggest discontinuation of the treatment for the participant.

In the case of the proven effectiveness of the exercises provided by the app in managing CLBP, access to the effective app version for participants in the control group after the end of the study period was provided.

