#### Intervention group: m-health-based pain education and exercise

Patients allocated to the experimental group received a login and password for individual access to the smartphone app (www.mysafebackapp.web.app/). Before the intervention begins, participants received a yoga mat, an elastic band, and a link to a tutorial video showing how to use the app functions. The app content for this group included three components: (1) a physical exercise program of 8 weeks, (2) weekly messages, and (3) an online booklet.

The exercise component (app “training” function) included 8 weeks of training, with two sessions per week (non-consecutive days) of core strengthening exercises. The exercise program was developed by exercise professionals with at least 5 years of clinical experience, specialists in chronic pain treatment, and who used exercise-based treatment. The training periodization followed the progression of pre-established protocols for CLBP treatment reported in the literature (see training periodization in Additional file 3) [49–52]. The exercises performed in each stage are presented in Additional file 4.

The app provided animated Graphics Interchange Format (GIFs), descriptions, and audio of how to perform each exercise. The number of repetitions or time under tension for each exercise were prescribed with a range of target zones (e.g., 10–12 repetitions, 20–30 s). For those who cannot reach these zones, they were asked to indicate (on the app) that they could not perform the complete exercise. Exercise sessions were carried out remotely and self-managed by the participant (i.e., the participants were responsible for carrying out the exercises). The content of the training sessions was made available (visible in the app version) each week of intervention training.

The message component from the app provided 8 messages (one per week), with the contents taken from the online booklet. Messages included information about the benefits of exercise, motivation, and positive messages about coping with pain.

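### The harms section promises a number of adverse events, but its two closed weekly questions yield participant-weeks with any complaint, so yes answers should not be reported as event counts

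*Protocol article*

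**What the plan says.** All of the relevant text is in the protocol article under Harms, ancillary, and post-trial care. The measure comes first: "The adverse events were collected by weekly recording the number of adverse events throughout the intervention period". The instrument follows: "A closed-ended question with two options (yes or no) sent by the app at the end of each week". Its wording is "During the last week of the study, did you present any different symptoms or worsening of the initial condition". A yes leads to a second closed question, "Do you think this symptom or worsening of the initial condition was generated by the treatment provided in this study".

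The section then says "At least two researchers discuss all adverse events", with medical consultants and experts if necessary. If the treatment is making the participant worse, "a video call is offered with one of the study physiotherapists to evaluate the issue", or discontinuation may be suggested. It does not say that every yes leads to a contact, or that the number, type or severity of events is written down at either step.

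Two other places set the scale. The intervention section says the exercise component "included 8 weeks of training, with two sessions per week (non-consecutive days) of core strengthening exercises", and the sample size section says "a minimum of 66 individuals would be required in the present study".

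**The concern.** The measure named in the first sentence is a count of events. The printed questions return a binary answer per participant per week. A yes does not show whether there was one problem or several, or whether it is new or was already reported the week before. The reference point is the condition at entry, not the previous week, so a participant who becomes worse in week 1 and stays worse can correctly answer yes at every later prompt. In the other direction, three separate problems in one week produce one yes, and the follow-up question speaks of a symptom in the singular.

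At stake is the harms statement for a remote, self-managed exercise programme in a trial without a data monitoring committee. If yes answers are totalled and labelled adverse events, readers will take the figure for something it does not measure, and a between-arm ratio of such totals will not be a ratio of event rates.

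**Working it through.** The article states no harms figure, so there is none to reproduce. The check has two parts.

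**1. What the questions can return (from the text alone)**

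- One binary answer per weekly prompt and 8 weeks of intervention give at most 8 yes answers per participant.
- For 66 participants: 66 × 8 = 528 participant-weeks. With an even 1:1 split: 33 × 8 = 264 per arm.
- *k* events in one week give 1 yes. One symptom or worsening present in *k* weeks can give *k* yes answers.
- A total of yes answers therefore equals the number of events only if no participant has more than one event in a week and no event spans two prompts.

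**2. How far yes-weeks can depart from events (illustration on assumed inputs)**

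The documents give no event rate or duration. Assume that new events are Poisson with rate λ per participant-week, that each is present for *D* weekly prompts, and that every prompt is answered. Over 8 weeks:

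- expected events = 8λ
- P(yes in week *w*) = 1 − exp(−λ · min(*w*, *D*))
- expected yes-weeks = the sum of these over *w* = 1 to 8

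Ratio of yes-weeks to true events:

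| λ | *D* = 1 | *D* = 2 | *D* = 3 |
|---|---|---|---|
| 0.05 | 0.98 | 1.79 | 2.45 |
| 0.1 | 0.95 | 1.71 | 2.29 |
| 0.2 | 0.91 | 1.56 | 2.01 |
| 0.5 | 0.79 | 1.20 | 1.42 |
| 1.0 | 0.63 | 0.84 | 0.90 |

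Example, λ = 0.1 and *D* = 2: events = 8 × 0.1 = 0.8; yes-weeks = 1.364; ratio = 1.364 / 0.8 = 1.71. Last row, *D* = 2: (0.632 + 7 × 0.865) / 8 = 0.84; *D* = 3: (0.632 + 0.865 + 6 × 0.950) / 8 = 0.90.

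So the error can go either way. It is 2% to 5% when events are rare (λ of 0.05 to 0.1) and confined to one week.

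A comparison between arms is affected too. With single-week events (*D* = 1), a true rate ratio of 2.0 would appear as (1 − e^−0.2) / (1 − e^−0.1) = 1.90 for rates 0.1 and 0.2. It would appear as 1.78 for 0.25 and 0.5, and as 1.61 for 0.5 and 1.0.

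**The case against.** The case on the other side is substantial, and much of it stands.

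- **The questions are not the whole process.** There is an attribution question, a review of adverse events by at least two researchers, and a video call in cases of deterioration. These may bring out what happened and how bad it was. This stands, and a reader should not infer that the reviewers have nothing to discuss. But the call is conditional, and the text states no record from either step that would turn yes answers into a number of events.
- **This is a condensed article.** Event forms, severity grading and episode definitions are commonly left to the full protocol or the analysis plan. This stands, so their absence is not the point here. The point is that the article prints both questions in full and describes the result as a number of events.
- **The count need not be wrong.** This also stands: it is nearly right if events are rare and brief.
- **A bias towards exercise looking safer is not shown.** A reader might infer that unrelieved back pain in the education arm would inflate its count. The question asks about different symptoms or worsening, so stable, unimproved pain should be answered no. Only persistent worsening is counted repeatedly, and nothing in the article says which arm would have more of it.
- **The data can tell repeat answers from different people.** Participants have individual logins, and the article nowhere says that yes answers will be summed over people and weeks. A reader might infer that a few people with a lasting symptom could not be told apart from many people with one bad week each. The answers as collected do separate these cases, and the fix relies on that.

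**Conclusion.** The mismatch is real and lies within one section: the stated measure is a number of adverse events, and the described questions can give only participant-weeks with any different symptom or worsening. Treating yes answers as events could overstate or understate harms. The range of 0.63 to 2.45 rests entirely on the assumed rates, durations, Poisson occurrence and complete answering. It shows that both directions are possible and does not predict this trial's error.

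The documents do not support saying that the harms figure will be wrong, that it will favour one arm, or that the trial can say nothing about safety. Labelled as what they are, the weekly answers with the participant's attribution form a usable, if coarse, harms summary.

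The correction is worth making but limited in reach. Adverse events are not among the listed co-primary or secondary outcomes, and sample size, alpha, power and the main comparisons are untouched.

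**What to change.** In the harms section and in the results report, replace the reference to a number of adverse events with two measures, each by arm:

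1. participants with at least one yes;
2. the proportion of answered participant-weeks with a yes, showing the number of prompts answered.

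Give both overall and restricted to complaints that the participant attributed to the treatment. Do not label yes answers as event counts. Report distinct events, their type or their severity only where records from the researchers' review or the video calls exist, and say how many of the yes answers such records cover.

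The cost is a reworded paragraph and a simple tabulation of data already collected. The small downside is that the harms figure becomes a proportion of participants or weeks instead of an event count. Two limits remain. The single combined question cannot be split afterwards into new symptoms and worsening. And because the article says the trial was conducted until August 2023, extra app fields after a yes (number, description, new or continuing, severity) could serve only future use of the app.

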##### Dissemination policy

After completing the study, we aim to disseminate the results to as many stakeholders as possible. First, participants will receive their reports with their measurements and interpretations in language adapted to the lay public’s understanding. The main findings, whether positive, negative, or inconclusive, will be disclosed directly or at an event aimed at managers of public security organizations through the exhibition/presentation of a structured summary (infographic) and submitted to a peer-reviewed international journal for possible publication. All information regarding the full protocol, participant-level dataset, and statistical code will be available from the corresponding author upon reasonable request.

## Discussion

This randomized control trial will investigate a new model of care to treat a highly prevalent and disabling problem in public safety workers, such as police and firefighters. We hypothesize that the m-health-based telerehabilitation program will benefit public safety workers with CLBP by reducing pain intensity and improving function and psychological, behavioral, and neuromuscular outcomes compared to a mobile minimal intervention approach (booklet).

The app is based on relatively simple interventions (i.e., remote-based exercise and pain education). This app was designed to be simple and have easy implementation in the worker health settings of public safety institutions. Some public safety institutions do not have, or only provide, in-person hospital care in a single location. Thus, the app developed will be able to expand care and potentially change the lives of millions of police officers and firefighters with CLBP that have limited access to face-to-face care.

In case of our hypothesis being confirmed, we can contribute to the discussion of a new treatment modality (i.e., m-health-based telerehabilitation program) for this population. The results may have practical applications to public security organizations that implement this therapeutic modality in CLBP treatment and may imply the reduction of absenteeism and presenteeism of these professionals, with a positive impact on the service provided to society.

